### Outcomes and Measures

The outcome evaluation of the implementation program was based upon the RE-AIM framework [18]. This framework describes implementation success as a combination of reach, intervention effectiveness, adoption, implementation, and maintenance. In addition to the instruments that were selected based upon the RE-AIM framework, the questionnaires described in Assessment of Barriers and Facilitators and Process Evaluation sections were also used as outcome measures.

*Reach* was measured by the proportion of service users who received Cognitive Adaptation Training in each team and by comparing these numbers between the 2 treatment arms. To detect possible selection bias, the representativeness of service users who received Cognitive Adaptation Training in the intervention condition was determined by comparing their demographic variables to those of the service users in the entire study population.

*Intervention effectiveness* refers to the clinical improvement of the service users as a result of Cognitive Adaptation Training. The effectiveness of Cognitive Adaptation Training was determined by the improvements of the service users on daily functioning and cognitive functioning measured by 2 observational questionnaires: Life Skills Profile [34] and the Nurses’ Observation Scale of Cognitive [35]. The Life Skills Profile consists of 39 questions on a 4-point scale (total score range: 39-156) and measures various aspects related to daily life activities: self-care; nonturbulence; social contact; communication; and responsibility. Results on the Life Skills Profile from the previous research [7] evaluating the effectiveness of Cognitive Adaptation Training revealed a significant effect for people receiving Cognitive Adaptation Training in addition to treatment as usual compared to treatment as usual only. The Nurses’ Observation Scale of Cognitive Abilities [35] measures cognitive functioning and includes 39 items (total score range: 0-121) subdivided into 8 cognitive domains (subscales): attention, perception, memory, orientation, higher cognitive domains, thoughts, language, and praxis. The Nurses’ Observation Scale of Cognitive Abilities is scored on a 4-point scale. Both the Life Skills Profile and Nurses’ Observation Scale of Cognitive Abilities have good psychometric properties [36,37].

*Adoption* was defined as the representativeness of participating sites and intervention agents that adopted the intervention. It is measured at the system level by comparing the determinants of the MIDI across the 2 implementation conditions.

*Implementation* refers to the Cognitive Adaptation Training specialists’ fidelity to the elements of Cognitive Adaptation Training as described in the Cognitive Adaptation Training protocol. The level of implementation was measured by the CAT Fidelity Scale.

*Maintenance*, or sustainability of the intervention was evaluated at follow-up, which was 6 months after the final contact with the implementation researchers. Maintenance was measured by comparing the differences between postmeasurement and follow-up of the abovementioned constructs (reach, intervention effectiveness, adoption, and implementation) between the 2 conditions.

Demographic information was obtained from both service users (birth year, gender, nationality, level of education, main diagnosis, age of onset) and the team members (date of birth, gender, nationality, level of education, years working experience, years working with the target group population, years working in current team) and was completed at baseline assessment.

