### Sample Size

Sample size was estimated for both intervention effectiveness of Cognitive Adaptation Training (based upon the Life Skills Profile) as well as implementation effectiveness (based upon the outcome variable Reach). To ensure enough power for both purposes, we used the highest estimated sample size. For intervention effectiveness, with a mean difference of 6 points on the Life Skills Profile (considered clinically relevant according expert opinions) and a standard deviation of 10.5 (based on the effectiveness trial of Cognitive Adaptation Training in residential settings [7], 78 service users needed to be included to detect significant improvements on the Life Skills Profile with a power of .8 and a significance level of .05. Accounting for a conservative attrition rate of 20%, a minimum of 98 service-users needed to be included in the study. For implementation effectiveness, based upon previous implementation research in the Netherlands [16], the expected proportion of service users reached in the experimental condition was set at 30%, compared to 5% in the control condition. To be able to detect a difference between conditions in proportion of service users reached with Cognitive Adaptation Training (with α=.05 and a power of .8), both groups (control and experimental) required a caseload of at least 34 service users each.

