### Statistical Analyses

To measure demographic and baseline differences between the 2 groups, chi-square tests will be performed for categorical variables, and 2-tailed independent sample *t* tests will be performed for continuous variables using SPSS software (version 24.0; IBM Corp). To assess the implementation effectiveness over time (outcome evaluation), mean differences in outcomes between the 2 arms on the dimensions of the RE-AIM framework were assessed using multilevel modelling [40]. A 3-level model will be built with team (level 3), subjects (level 2), and assessment (level 1) entered as levels. Significance of the fixed regression effects will be tested using the 1-tailed independent sample *t* test (=.05). The content of the focus group meetings and process evaluations will be transcribed verbatim and analyzed using a combined approach of inductive and deductive thematic analysis in ATLAS.ti (version 8.0; ATLAS.ti Scientific Software Development GmbH).

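### The selection-bias check on who receives Cognitive Adaptation Training compares demographics only, so daily and cognitive functioning are not examined directly although both are scheduled at baseline

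*Protocol article*

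**What the plan says.** All references are to the protocol article.

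- **Purpose and method of the check (Outcomes and Measures, Reach).** Reach itself is the proportion of service users in each team who received CAT. A separate sentence adds a check that is meant to reveal selection among recipients in the experimental arm. How representative they are "was determined by comparing their demographic variables to those of the service users in the entire study population".
- **What counts as demographic (same section).** "Demographic information was obtained from both service users (birth year, gender, nationality, level of education, main diagnosis, age of onset"). Main diagnosis and age of onset are clinical items, but no item scores functioning or cognition.
- **What else is measured at baseline (Table 1).** LSP and NOSCA are scheduled for service users at T0 and T3, in rows separate from demographic information. Outcomes and Measures describes their role as capturing "improvements of the service users on daily functioning and cognitive functioning measured by 2 observational questionnaires".
- **What CAT is tailored to (Cognitive Adaptation Training).** Individual plans draw on a functional assessment, cognitive tests and a behaviour-type rating.
- **The only other baseline comparison (Statistical Analyses).** "To measure demographic and baseline differences between the 2 groups, chi-square tests will be performed" for categorical variables, with t tests for continuous ones. The two groups are the trial arms.

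**The concern.** A check for selection should look at the characteristics on which selection is most plausible. CAT addresses functional problems that arise from cognitive deficits, so functioning and cognition are the natural candidates. Recipients could be the more able users, who are easier to work with, or the most impaired, who seem to need it most. Eligibility excludes only outpatients and minors, and the Sample Size section expects 30% to be reached in the experimental condition, so most eligible users are expected not to receive CAT.

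Followed as written, the check could find recipients demographically similar to the study population and call them representative, without anyone having looked at baseline functioning. At stake are what can be said about whom the programme reached, and how far the results on LSP and NOSCA generalise.

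**Working it through.** **1. Can the text be read to include the T0 scores?**

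| Place | Who is compared | Variables |
|---|---|---|
| Outcomes and Measures, Reach | CAT recipients in the intervention condition v entire study population | Demographic |
| Outcomes and Measures, demographic paragraph | – | Six items, no functioning or cognition score |
| Table 1, service user | – | Demographics, LSP and NOSCA in separate rows, all at T0 |
| Statistical Analyses | Arm v arm | Demographic and baseline |

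Table 1 keeps the scales apart from the demographics. Statistical Analyses adds the word baseline for the arm comparison, while the Reach sentence does not. The arm comparison cannot stand in for the check, because it says nothing about recipients against others. So T0 LSP and NOSCA are outside the check as stated.

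**2. The plan's own figures used as context.** The plan gives no sample size for this check. Its LSP calculation uses a difference of 6 and an SD of 10.5, so d = 6/10.5 = 0.571. At 80% power and alpha .05, a one-sided t-based calculation gives 38.56, rounded up to 39 per arm, or 2 × 39 = 78 in total, as stated. Allowing for 20% attrition, 78/0.8 = 97.5, so 98, also as stated. The point does not depend on these figures; 98 serves below as the planned minimum.

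**3. Illustration of what each comparison could detect.** These assumptions are not in the document:

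- Recipients differ from other users by D = 0.5 SD on T0 LSP. At SD 10.5 this is 0.5 × 10.5 = 5.25 points, close to the 6 points that the plan treats as clinically relevant.
- A continuous demographic has correlation r = 0.1 to 0.3 with LSP and is linked to selection only through LSP. Its expected difference is then r × D = 0.05 to 0.15 SD.
- Two-sided t test at .05, clustering ignored.

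Group sizes:

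- Planned minimum: 98 users, 49 per arm, 30% reached, so 0.30 × 49 = 14.7, about 15 recipients. The others number 49 − 15 = 34 within the arm, or 98 − 15 = 83 in the whole study.
- Larger case (assumed): 200 experimental-arm users, 30% reached, so 60 v 140.

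Power comes from the noncentral t distribution with noncentrality d × √(n₁n₂/(n₁+n₂)). For example, 0.5 × √(60 × 140/200) = 3.24.

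| Recipients v others | T0 LSP directly, d = 0.5 | Demographic, d = 0.05 | d = 0.10 | d = 0.15 |
|---|---|---|---|---|
| 15 v 34 | 0.352 | 0.053 | 0.062 | 0.076 |
| 15 v 83 | 0.423 | 0.054 | 0.064 | 0.083 |
| 60 v 140 | 0.897 | 0.062 | 0.099 | 0.162 |

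With a larger gap of 0.8 SD (8.4 points) at 15 v 83, the direct comparison has 0.806. A demographic correlated 0.1 to 0.3 has 0.059 to 0.135, and one correlated 0.5 has 0.292.

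The direct comparison is far stronger in every row, but its absolute power depends heavily on how many users are enrolled.

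**The case against.** **This is an addition, not an error, and an article may leave it to a fuller document.** Partly right: there is no contradiction and no wrong calculation. But the article does name the class of variables for this check, and that class fits its stated purpose poorly. This is a choice fixed too narrowly rather than an omitted detail.

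**Selection by staff is not documented.** This stands. A reader might infer that team members choose whom to offer CAT. The article says that team members provide it and that goals are set by shared decision-making; it gives no rule for who is offered it. Selection on functioning is a plausible inference only.

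**The effectiveness results are not biased.** This stands. A reader might infer that hidden selection would distort the LSP and NOSCA comparison. The planned analysis contrasts randomised arms in a multilevel model, and who receives CAT within an arm does not bias that contrast. A reader might likewise take representativeness as part of the Reach estimate; Reach is a proportion, and no planned estimate of it changes.

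**Such selection would not be wholly invisible.** This stands. Education, main diagnosis and age of onset are partial proxies, and several variables give more chance of a signal than the single continuous one in the illustration. The accurate statement is that functioning is not examined directly.

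**The power figures are fragile.** This stands. The 90% needs 60 v 140; at the planned minimum it is 35% to 42%. Nor are figures that ignore clustering generally upper bounds: recipients and others share teams, so with similar reach across teams, accounting for team can raise power.

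**Conclusion.** The point holds as a weakness in the content of the check, worth correcting because the remedy is nearly free. The article sets out to detect selection bias among CAT recipients and compares six demographic items. It leaves out the two scheduled baseline measures closest to what CAT targets, and no other comparison in the article supplies them.

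The consequence is confined to the claim that those reached are representative and to how far the effect generalises. The estimate of Reach and the randomised contrast on LSP and NOSCA are unaffected.

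The size is illustrative: for a 0.5 SD difference, about 35% to 90% power for the direct comparison against roughly 5% to 16% for a single weakly correlated demographic. It rests on the assumed gap, correlations and group sizes, with clustering ignored. The textual finding does not depend on these numbers.

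**What to change.** Add T0 LSP total and T0 NOSCA total to the variables in the representativeness check, alongside the demographics. Report standardised differences with team accounted for; these remain informative where the number of recipients is too small for a test to be useful. State how many users lack T0 scores among recipients and among those they are compared with. Base the statement on representativeness on both sets of variables.

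The cost is two more rows in a planned table. Both scales are already scheduled at T0, so no new data collection is needed, and the article reports that data analysis is still under way.

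### The selection check for Reach compares experimental-arm recipients with a population that includes them and the control arm, so it understates selection within teams

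*Protocol article*

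**What the plan says.** The Reach paragraph of Outcomes and Measures states an aim, a group and a comparator. The aim is "To detect possible selection bias". The group is given in the phrase "the representativeness of service users who received Cognitive Adaptation Training in the intervention condition". The method is "comparing their demographic variables to those of the service users in the entire study population". Nothing elsewhere in the article narrows the comparator to non-recipients or to the experimental teams.

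The Sample Size section gives the planning value that fixes how large the recipient group should be: "the expected proportion of service users reached in the experimental condition was set at 30%, compared to 5% in the control condition".

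Three other statements bear on the point. Recruitment and Allocation says that teams, or clusters of teams, were randomised. Setting reports 21 teams in 4 institutions, each helping 9 to 35 service users. The Implementation Program section says that the first phase, including the CAT training, was the same in both arms, so control teams could also deliver CAT.

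**The concern.** CAT is delivered by a team's own members to the service users in their care, so any selection takes place inside teams. The informative contrast is between those who received CAT and those whom the same teams did not reach. The stated comparator departs from this in two ways.

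- Recipients are part of the group they are compared with, which pulls the difference towards zero.
- About half of the comparator, if the arms are of similar size, are control-arm users who were never available to the experimental teams. Any demographic difference between the arms enters the comparison as though it concerned selection.

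Reach is one of the primary outcomes, and this is the only check on the representativeness of the service users reached that the article states. A small difference could be reported as reassurance when teams had in fact favoured certain users.

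**Working it through.** **Planning figure.** The plan states no figure for the selection check itself. The nearest is the Reach sample size: "with α=.05 and a power of .8", "both groups (control and experimental) required a caseload of at least 34 service users each". For 30% against 5%, two-sided with unpooled variance, n = (1.960 + 0.842)² × (0.30×0.70 + 0.05×0.95) / 0.25² = 7.85 × 0.2575 / 0.0625 = 32.3, so 33 per group. The pooled version gives 36, and 34 per group has two-sided power 0.787. The figure reproduces closely enough, and 30% is used below as the plan's own reach.

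**Notation.** r is reach in the experimental arm. D is the recipient mean minus the non-recipient mean in that arm. d is the control-arm mean minus the experimental-arm mean. w is the control arm's share of all service users.

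**Algebra.**

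1. Recipients minus the whole experimental arm = (1 − r)D.
2. Whole-population mean = experimental-arm mean + w·d.
3. Planned contrast = (1 − r)D − w·d. With equal arms (assumed), w = 0.5.

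The dilution factor 1 − r does not depend on arm sizes; only the weight on d does.

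| Reach r | Share of D shown if d = 0 | d that would cancel D fully (equal arms) |
|---|---|---|
| 10% | 0.90 | 1.8 D |
| 30% | 0.70 | 1.4 D |
| 50% | 0.50 | 1.0 D |
| 70% | 0.30 | 0.6 D |

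At 30% reach and equal arms, recipients make up 0.30/2 = 15% of the comparator. The factor 1 − 0.15 = 0.85 is the shrinkage relative to recipients against everyone else in the study, controls included. Relative to the within-arm contrast it is 0.70.

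**Simulation.** The assumptions, none given in the article, are 11 experimental and 10 control teams, 20 users per team, 30% reach in every experimental team, a normally distributed characteristic and an intracluster correlation (ICC) of 0 to 0.2. There were 2,000 runs per setting, tested at the two-sided 5% level. The planned comparison was tested as two independent groups. The within-team contrast was a one-sample t test on the team differences. Power is under modest selection, with a mean within-team difference of 0.25 to 0.32 SD.

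| ICC | False positives: planned | within team | Power: planned | within team |
|---|---|---|---|---|
| 0 | 2.8% | 5.2% | 37% | 51% |
| 0.05 | 2.8% | 5.1% | 33% | 48% |
| 0.1 | 4.1% | 5.1% | 33% | 47% |
| 0.2 | 5.8% | 5.4% | 30% | 42% |

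At ICC 0 the mean planned contrast was 0.224 against 0.320 within teams, a ratio of 0.70, as the algebra gives. Simply removing recipients from the comparator while keeping the control arm is not enough: the false-positive rate then rose from 5.3% at ICC 0 to 10.3% at ICC 0.2.

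**The case against.** Comparing a subset with the whole is a normal way to describe representativeness, and the article assigns no test to this check. The chi-square and t tests in Statistical Analyses are for differences between the two arms. If the overlap were handled with the correct variance, the dilution alone would cost no information within the experimental arm, since (1 − r)D is only a rescaling of D. This stands for the descriptive use. It does not remove the mismatch with the stated aim of detecting selection bias: a difference read at face value, or tested as two independent groups, is understated. If the whole population were taken to mean the experimental arm alone, the arm term would vanish but the factor 0.70 would remain.

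A reader might infer that the check will invent selection. The documents do not support that. Overlap can only shrink the contrast and never changes its sign. Apparent selection needs a chance imbalance between arms, which has expectation zero under randomisation, and the simulated false-positive rate stayed between 2.8% and 5.8%.

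A reader might also infer that real selection could vanish altogether. That needs a large imbalance in one particular direction. Take recipients aged 47 and non-recipients aged 51.3, so that D = −4.3 and the arm mean is 0.3×47 + 0.7×51.3 = 50.0. A control mean of 44 gives a population mean of 47 and a planned difference of zero. With an assumed age SD of 12, 20 users per team and 10.5 teams per arm, the standard error of the arm difference is √(2×144×(1 + 19×ICC)/210): 1.6 years at ICC 0.05 and 2.6 at ICC 0.2. The 6-year gap is then about 3.7 or 2.3 standard errors. Merged clusters would raise the standard error somewhat. A one-standard-error gap moves the planned difference from 0.70×4.3 = 3.0 years to between 2.2 and 3.8, or between 1.7 and 4.3. Partial distortion is realistic; full cancellation is an extreme case. The planned baseline comparison of the arms would also bring a large gap into view.

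**Conclusion.** The point holds as a minor one. The comparator is a stated choice that fits its stated purpose poorly. At the planned 30% reach the check shows about 0.70 of the within-arm difference when the arms are alike, and less as reach rises. With equal arms it also carries half of any chance arm difference. Under the simulation's assumptions, power to detect modest selection was 30–37% for the planned comparison tested as independent groups, against 42–51% within teams. Both are low.

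The 0.70 rests only on the plan's 30% and on alike arms. The half-weight rests on equal arms. The power figures rest on assumed team size, ICC and strength of selection.

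A reader might infer that the Reach result itself is biased. It is not: Reach is the proportion of service users receiving CAT, compared between arms, and this check enters neither that estimate nor its test.

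**What to change.** In the Reach paragraph, define the selection check as a comparison of recipients with non-recipients within the experimental arm, with team as a stratum or random effect. Report the same contrast descriptively in the control arm, where few recipients are expected at 5% reach. Keep the comparison with the whole population if wanted, labelled as a description of representativeness and not as the test for selection.

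The cost is a change of wording and a short extra analysis. Outcomes and Measures says that the demographic data were collected at baseline, and Results says that analysis was still under way, so no new data are needed.

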### Recovery-Oriented Practice

To measure the extent to which the teams provided recovery-oriented care in general, the translated Dutch version of the Recovery Oriented Practices Index [38] was used. It consists of 26 items on a 5-point scale (total score range: 0-130), measuring 8 domains of recovery-oriented care. The domains include meeting basic needs; comprehensive services; network supports and community integration; service user involvement and participation; strengths-based approach; customization and choice; self-determination; recovery focus. The Recovery Oriented Practices Index was administered and scored by one of the researchers through an interview with the management of the rehabilitation teams. The construct validity of the Recovery Oriented Practices Index has been reported as good [39].

### Sample Size

Sample size was estimated for both intervention effectiveness of Cognitive Adaptation Training (based upon the Life Skills Profile) as well as implementation effectiveness (based upon the outcome variable Reach). To ensure enough power for both purposes, we used the highest estimated sample size. For intervention effectiveness, with a mean difference of 6 points on the Life Skills Profile (considered clinically relevant according expert opinions) and a standard deviation of 10.5 (based on the effectiveness trial of Cognitive Adaptation Training in residential settings [7], 78 service users needed to be included to detect significant improvements on the Life Skills Profile with a power of .8 and a significance level of .05. Accounting for a conservative attrition rate of 20%, a minimum of 98 service-users needed to be included in the study. For implementation effectiveness, based upon previous implementation research in the Netherlands [16], the expected proportion of service users reached in the experimental condition was set at 30%, compared to 5% in the control condition. To be able to detect a difference between conditions in proportion of service users reached with Cognitive Adaptation Training (with α=.05 and a power of .8), both groups (control and experimental) required a caseload of at least 34 service users each.

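### The 80% power stated for the Life Skills Profile assumes a full 6-point difference between groups, which does not fit an arm comparison in which 30% versus 5% of users are expected to receive the intervention

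*Protocol article*

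**What the plan says.** The Sample Size section bases the Life Skills Profile (LSP) calculation on this effect: "with a mean difference of 6 points on the Life Skills Profile (considered clinically relevant according expert opinions"). For the spread it takes this value: "a standard deviation of 10.5 (based on the effectiveness trial of Cognitive Adaptation Training in residential settings"). Its conclusion is that "78 service users needed to be included to detect significant improvements on the Life Skills Profile with a power of .8 and a significance level"; the level given is 0.05. On dropout it says: "Accounting for a conservative attrition rate of 20%, a minimum of 98 service-users needed to be included in the study". The larger of two estimates was to be used. The Reach estimate is 34 per group (68 in total), so the LSP figure sets the trial's size.

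For Reach, the same section states that "the expected proportion of service users reached in the experimental condition was set at 30%, compared to 5% in the control condition". Outcomes and Measures defines Reach as the share of each team's service users who received Cognitive Adaptation Training.

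Outcomes and Measures says that intervention effectiveness "refers to the clinical improvement of the service users as a result of Cognitive Adaptation Training", measured by the LSP and the nurse-rated cognitive scale (NOSCA). The Abstract lists it among the primary outcomes. On the analysis, Statistical Analyses states that "mean differences in outcomes between the 2 arms on the dimensions of the RE-AIM framework were assessed using multilevel modelling". On the test, which is a t test, it states: "Significance of the fixed regression effects will be tested using the 1-tailed independent sample".

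The Implementation Program section gives the same phase 1, training included, to every team. The arms differ in later implementation support.

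**The concern.** The 6 points and the Reach figures cannot both describe the same arm comparison unless recipients gain far more than 6 points. The SD comes from the earlier effectiveness trial, whose LSP contrast was the intervention added to usual treatment against usual treatment alone. In the present trial most users in both arms are expected not to receive the intervention, so any benefit to recipients is averaged over a majority of non-recipients. The calculation makes no allowance for this.

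The stake is how a primary outcome is interpreted. A reader who accepts 80% power could take a non-significant LSP difference as adequate evidence against the intervention, although that result would be likely even if recipients gained the full 6 points.

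**Working it through.** **Inputs.** From Sample Size: difference 6, SD 10.5, power 0.80, alpha 0.05, attrition 20%, Reach 30% and 5%. From Statistical Analyses: one-sided test. From Setting: 21 teams with 9 to 35 users each, so 189 to 735 users. Assumed: equal arms, as the Reach calculation uses; a baseline correlation of 0.7 where stated; no gain in non-recipients.

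**1. Reproducing the plan's figure.** A one-sided two-sample t test with 6/10.5 = 0.571 SD has power 79.5% at 38 per arm and 80.4% at 39 per arm. So 2 × 39 = 78, and 78/0.8 = 97.5, rounded up to 98. Other readings do not give 78: the two-sided version needs about 49 per arm (98 before attrition), and a single-group before-after calculation needs about 19 to 24. The plan's figure is therefore a contrast of two groups a full 6 points apart.

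**2. Arm difference implied by Reach.** Arm difference = (0.30 − 0.05) × gain per recipient.
- Gain 6: 0.25 × 6 = 1.5 points (1.5/10.5 = 0.14 SD).
- Gain 12: 0.25 × 12 = 3 points.
- For an arm difference of 6: 6/0.25 = 24 points per recipient (24/10.5 = 2.3 SD).

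**3. Power.** With n per arm, power ≈ Φ(δ / (SD × √(2/n)) − 1.645). At n = 39 and δ = 1.5 the standard error is 10.5 × √(2/39) = 2.378; 1.5/2.378 = 0.631; Φ(−1.014) = 0.155. Baseline adjustment at r = 0.7 replaces the SD by 10.5 × √(1 − 0.49) = 7.50. One-sided t-test results, before clustering:

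| Users analysed | 1.5 points | 1.5 points, r = 0.7 | 3 points | 3 points, r = 0.7 |
|---|---|---|---|---|
| 78 | 15.4% | 22.1% | 34.7% | 54.2% |
| 98 | 17.3% | 25.4% | 40.5% | 62.6% |
| 189 | 25.3% | 39.2% | 62.2% | 86.3% |
| 735 | 61.4% | 85.6% | 98.7% | >99% |

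The 98 row assumes no attrition; with the planned 20% the 78 row applies. Two-sided power for 1.5 points, unadjusted, is about 9% at 78 and 10% at 98. For 80% one-sided power at 1.5 points, unadjusted, n per arm ≈ 2 × (1.645 + 0.842)² × 10.5²/1.5² ≈ 606, about 1,212 in total.

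**4. Clustering, illustrated.** At 35 users per team the design effect is 1 + 34 × ICC. With an assumed ICC of 0.01 it is 1.34, so 735 users count as about 549, and the 85.6% falls to about 76%. With 0.05 it is 2.7, about 272 users, and power is about 50%.

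**5. Recipients versus non-recipients.** Average Reach is (0.30 + 0.05)/2 = 0.175. Of 78 users about 14 are recipients, of 98 about 17. One-sided power for 6 points is about 60% and 69%.

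**The case against.** The strongest reply is that the article calls 6 points clinically relevant and never says it is the gain per recipient. The 1.5 points therefore depends on premises the plan does not state. This stands, and the result has to be shown as a range. It does not rescue the 80%: as an arm difference, 6 points needs 24 points per recipient, and at 78–98 users even 12 points per recipient falls short, adjusted or not.

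Second, 98 is a minimum, and 21 teams were included. This also stands. A reader might take the unadjusted 61% at the maximum caseload as a ceiling, but it is not one: baseline adjustment at r = 0.7 gives about 86%, and a larger gain per recipient gives more. These figures precede clustering and attrition, and the article does not say how many users were assessed. Its own 80% is attached to 78 and 98.

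Third, the outcome is defined as improvement resulting from the intervention, so a recipients-only contrast may have been meant, and a condensed article may leave the analysis population to a fuller document. But the analysis statement compares the two arms on the RE-AIM dimensions, and comparing recipients with non-recipients would be neither randomised nor powered at 80% (60–69%).

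Two stronger readings are not supported. A reader might infer an arithmetic slip, but 78 and 98 are computed correctly from their inputs; the fault is the assumed difference. A reader might also infer that a null arm result is nearly certain. Even under the 1.5-point premise at 78–98 users, non-significance is about 83–85% likely unadjusted, and less so with baseline adjustment or more users.

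**Conclusion.** The point holds in this form: the 80% power stated for the LSP at 78 (98) users is not delivered for the between-arm comparison under the section's own Reach expectations. With 6 points per recipient and no gain in others, one-sided power there is about 15–17%, or 22–25% with an assumed r of 0.7. The direction is firm for any plausible gain per recipient at those numbers. The exact size is not, because it depends on the gain per recipient, the number assessed, the baseline correlation and the clustering, none of which the article fixes for this contrast. Some combinations of larger caseload, baseline adjustment and larger gain exceed 80% before clustering, so the documents do not show that the trial as conducted must be underpowered.

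A reader might also conclude that intervention effectiveness should be demoted to a secondary outcome. The documents do not support this. It is a declared primary outcome and data collection ended in January 2020, so demotion now would be a substantive change needing justification and disclosure.

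**What to change.** - Withdraw the 80% power claim for the between-arm LSP comparison. Restate power for the diluted difference as a range, giving the assumed gain per recipient, number of users assessed, baseline correlation and clustering.
- State that the randomised LSP and NOSCA comparison is between arms over all assessed service users.
- Report it as an estimate with an interval, and say that a non-significant result is not adequately powered evidence against the intervention.
- Label any comparison of recipients with non-recipients as non-randomised, and adjust it for the T0 score and the recorded demographics.
- Keep intervention effectiveness as a declared primary outcome.

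The cost is wording in the plan and the results report. No new data are needed, and the sample size can no longer change. The trial gives up a power statement that its own assumptions do not support.
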